#### Analysis

This is a feasibility study and it is not planned to test any statistical hypotheses with regard to any of the endpoints in a confirmatory sense. For the exploratory evaluation of our hypotheses, a two-sided 95% CI of adjusted treatment differences will be computed. However, the CIs will have to be interpreted in the perspective of the exploratory character of study, i.e., as an interval estimate for effects under these conditions. All statistical analyses will be performed using STATA version 14 (43).

### Participants

#### Inclusion Criteria

Subject receiving any first ICD-10 diagnosis of non-psychotic mental disorder (including Acute and Transient Psychotic Disorders) at SLaM (borough of Lambeth) between April 1^st^ 2018 and March 28^th^ 2018;Aged ≥14;Subject with a good understanding of spoken and written English.

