## Methods

This is a feasibility study which will evaluate essential real world parameters associated with the implementation of an electronic, clinically-based, individualized, transdiagnostic risk calculator for the detection of individuals at risk and the prediction of psychosis in secondary mental health care. Obtaining these figures is a necessary step in order to accurately estimate the resources (e.g., staffing) needed for the routine clinical use of the calculator. There are two phases in this study: an initial *in-vitro* (1 month) testing which does not involve patients contact and a second *in-vivo* piloting (11 months, total study duration 12 months), which involves recruitment of SLaM patients. Before we present the study design, we will briefly summarize the core characteristics of the transdiagnostic risk calculator.

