**Figure 3 F3:**
[figure not shown]
Flow chart of study design including the *in-vitro* and *in-vivo* phase.

The *in-vitro* phase will last 1 month.

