If the patient agrees to participate in the study, they will then be invited to undergo a refined assessment (step 3, Flow Chart), which includes the standard CHR-P assessment. Specifically, we will use the combined Comprehensive Assessment for At Risk Mental States (CAARMS, version 12/2006) (3) and Structured Interview for Prodromal-Risk Syndromes, version 5.0 (SIPS) (40), clinician-rated and iPad version, that have been developed in our department as part of previous ongoing studies.

At the end of this assessment, the researchers would communicate the results to the responsible clinicians (step 4, Flow Chart). In case the individuals would meet the standard intake criteria for a state of risk for psychosis (i.e., a CHR-P state), they would be referred to the local Clinical High Risk service [the OASIS (9)] for standard care as recommended by the NICE (41). If the individuals do not meet the intake criteria for a CHR-P state, the referrer will be informed, and standard care provided accordingly. Overall, there will be no change in the current standard care for any participants. This prototype will be piloted in all local secondary mental health services present in the borough of Lambeth, Lewisham, Croydon and Southwark.

Participants will be reimbursed for their participation in the study at an hourly rate of £10. For patients under the age of 16, their time will be reimbursed with Amazon gift vouchers, again to the value of an hourly rate of £10 per hour. Table 2 lists the study procedures.

**Table 2 T2:** Study procedures for individuals detected by the transdiagnostic risk calculator and referred by clinicians for an assessment for psychosis-risk.

		**Baseline**		**Follow-up**
	**Screening Visit**	**Day 1**	**Day 2 (2 weeks+- 3 days)**	**6 months +- 2 weeks**
Patient information and informed consent	**X**			
CHR-P assessment		**X**	**X**	**X**

*The in-vivo phase will last 11 months*.

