### Statistics

#### Sample Size

This is a feasibility study to investigate key implementation parameters for an electronic risk calculator. As such the study is neither designed nor powered to validate new tools or test specific hypotheses.

The primary outcome of the *in-vitro* phase is the development and integration of the transdiagnostic risk calculator in the local electronic health register. As such, no power calculation is made for the *in-vitro* primary outcome.

They key rate-limiting barrier toward a scalable use of the transdiagnostic risk calculator in the broader clinical scenario is the clinicians' adherence to the recommendations made by the calculator itself. Therefore, the primary outcome of the *in-vivo* phase of this study is the adherence of clinicians to the use of the calculator, defined by the proportion of clinicians who have responded to the prompts sent on the recommendation of the electronic risk calculator from SLaM secondary mental health care. The sample size calculation is therefore made for this primary outcome. In line with the NIHR guidance, our main outcomes are feasibility parameters, and sample size calculation is made for the expected level of precision (45). Assuming a predicted psychosis threshold of 5–10% (at 2 years), on the basis of the previous study (24), we expect to detect at least 120 at-risk individuals per 11 months recruitment in SLaM. Conservatively assuming that only half of SLaM clinicians would eventually respond to the alerts generated by the calculator, the anticipated sample size would allow us to have an acceptable (42) maximum margin of error of 0.1 (i.e., 95%confidence interval (CI) ±0.1) for adherence rates of clinicians >60%. The secondary outcomes of the *in-vivo* phase will measure other key feasibility parameters that are necessary to implement the calculator in the wider clinical routine: impact of different types of alerts on the clinicians' adherence to the recommendations made by the transdiagnostic risk calculator; raw number of referrals initiated from secondary mental health care clinicians for an assessment of psychosis-risk; qualitative reasons for any lack of clinicians' adherence.

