## Study Status

The study status is ongoing, and recruitment for the *in-vivo* phase commenced on 1 August 2018. The study has been approved by National Research Ethics Service (NRES) East of England - Cambridgeshire and Hertfordshire Research Ethics Committee (Ref: 18/EE/0066).

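### The index-diagnosis window in the inclusion criteria ends before it begins, and the intended dates cannot be recovered from the article

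*Protocol article*

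**What the plan says.** The Inclusion Criteria of the protocol article limit entry to people with a first non-psychotic ICD-10 diagnosis at the Trust "between April 1^st^ 2018 and March 28^th^ 2018".

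Four other statements in the article bear on the calendar:

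- Methods describes the in-vivo piloting as lasting "11 months, total study duration 12 months), which involves recruitment of SLaM patients".
- The In-vitro Phase section (line after Figure 3) says that this "phase will last 1 month", and the note under Table 2 repeats that "The in-vivo phase will last 11 months".
- Study Status reports that recruitment for the in-vivo "phase commenced on 1 August 2018".
- Sample Size rests on the same 11 months: "we expect to detect at least 120 at-risk individuals per 11 months recruitment in SLaM".

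The article does not give a second version of the window, and it does not say how the window for the diagnosis relates to the period in which patients are screened and alerts are sent.

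**The concern.** This is an operative eligibility rule. Under In-vivo Phase, the research team screens the register for patients meeting the study criteria, runs the calculator on them and alerts the responsible clinician when the threshold is reached. The date window therefore determines whose records are screened, and through them which clinicians receive a prompt. The primary in-vivo outcome is the proportion of clinicians who respond to those prompts.

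A window with no dates in it defines no population. A reader will assume a misprinted year, but the two single-year corrections describe different studies. One mixes diagnoses made before recruitment with new ones. The other uses only diagnoses made before recruitment. Someone reproducing the study, or judging whether the 120 expected detections are consistent with the eligibility rule, cannot tell which was meant.

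**Working it through.** **Inputs.** Window dates from Inclusion Criteria; in-vivo start of 1 August 2018 from Study Status; 11-month in-vivo phase, 1-month in-vitro phase and 12-month total from Methods and the phase descriptions; 120 detections per 11 months from Sample Size. Lengths are counted inclusively, and one month is taken as 30.4375 days.

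**Step 1: the window as printed.** 28 March 2018 minus 1 April 2018 = −4 days. No calendar date is on or after the start and on or before the end, so the eligible set is empty.

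**Step 2: the in-vivo phase.** Eleven months from 1 August 2018 run to about 30 June 2019: 365 − 31 = 334 days. The article does not print this end date; it follows from the start and the duration.

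**Step 3: the candidate repairs against that phase.**

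| Repair | Window | Length | Before 1 Aug 2018 | Overlap with in-vivo phase | In-vivo days left after window closes |
|---|---|---|---|---|---|
| End year 2019 | 1 Apr 2018 to 28 Mar 2019 | 362 days (11.9 months) | 122 days | 240 days | 94 days |
| Start year 2017 | 1 Apr 2017 to 28 Mar 2018 | 362 days (11.9 months) | 362 days | 0 days | all 334 days |
| Dates swapped | 28 Mar to 1 Apr 2018 | 5 days | 5 days | 0 days | all 334 days |

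Checks for the 2019 repair: 30 + 31 + 30 + 31 = 122 days from April to July 2018; 3 + 30 + 31 + 30 = 94 days from 29 March to 30 June 2019; 122 + 240 = 362; 240 + 94 = 334. As shares, 122/362 = 34% of the window precedes recruitment, and 94/334 = 28% of the in-vivo phase follows the window's close. Under the 2017 repair the window closes 126 days before recruitment starts.

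**Step 4: does the 2019 repair fit anything else in the article?** At 11.9 months it is close to the 12-month total. Taking off the in-vitro month (30 days, April 2018) leaves 1 May 2018 to 28 March 2019: 362 − 30 = 332 days, or 10.9 months, close to the planned in-vivo length. That pattern would fit a timetable that later slipped to August, but the article does not say so.

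**Step 5: what the ambiguity could mean for the 120, as an illustration only.** Assume that detections arise evenly over diagnosis dates, at 120 per 334 days. Under the 2019 repair, counting only diagnoses made during the in-vivo phase gives 120 × 240/334 = 86. Counting the whole window gives 120 × 362/334 = 130. The range of 86 to 130 depends entirely on that assumption and on which diagnoses count, and the article settles neither.

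**The case against.** The strongest reply is that this is a typing error with an obvious correction. Recruitment had already started when the article was written, so a working window presumably existed. Changing one digit in the end year gives a span close to the 12-month study. Much of this stands: 2019 is clearly likelier than 2017, and the fault looks typographical rather than a deliberate choice.

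It is also fair to say that the diagnosis window and the recruitment period are different things. A patient diagnosed in May 2018 can be screened in August. The 120 are detections during recruitment, and Sample Size ties them to no diagnosis window. This stands too, and it rules out several stronger conclusions that a reader might draw:

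- *That late patients would be wrongly excluded.* Diagnosis is followed by screening, alert, clinician decision, consent, assessment and a 6-month follow-up. Closing the diagnosis window before the phase ends could be intentional.
- *That older diagnoses bias adherence downwards.* The article says nothing about discharge of these patients or about how clinicians respond to alerts on older diagnoses. The mechanism is plausible but undocumented.
- *That the window ought to be 1 August 2018 to 30 June 2019.* No section requires the two periods to coincide, and the end date is inferred. Diagnoses made on the last days would leave no time within the phase for the later steps.
- *That the sample will fall short of 120.* The figure of 86 arises only if earlier diagnoses do not count, which the article does not state.

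None of this makes the printed criterion usable, and none of it tells the reader which dates were applied.

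**Conclusion.** The point holds in a limited form. The criterion is impossible as printed, by four days, and the article contains no correction; this is certain. Neither single-year repair coincides with an 11-month phase from 1 August 2018. The likelier one overlaps it for 240 of 334 days, the other not at all. These counts rest on the stated start date and on the 11 months running without interruption. Since the two periods need not coincide, the mismatch shows only that the intended window cannot be recovered from the document. No effect on the adherence estimate, in size or direction, can be inferred from it. The correction is still necessary, because the criterion defines the population behind the primary in-vivo outcome.

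**What to change.** Replace the printed dates with the index-diagnosis dates actually intended and used. Add a sentence reconciling them with the 1 August 2018 start and with the 11-month basis of the 120 expected detections. If diagnoses made before 1 August 2018 are included, state that this is deliberate and report adherence for those alerts separately from alerts on later diagnoses.

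If the dates in use are sound and only the print is wrong, the cost is a corrected line and, where earlier diagnoses are included, one extra descriptive breakdown. If the eligibility dates themselves have to change, the cost is higher. Recruitment is under way, patients already screened could be affected, and Ethics and Regulatory Approval requires a favourable ethics opinion before a substantial amendment is put into effect. For that reason the sponsor should document the window in use rather than adopt a new one to match the recruitment period.

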#### Exclusion Criteria

Present or past diagnosis of any ICD-10 psychotic disorder [excluding Acute and Transient Psychotic Disorders (44)];Any evidence of organic condition that may be responsible for psychotic symptoms.

#### Withdrawal of Subjects

If an individual decides to take part in the study, they will still be free to withdraw at any time, without giving a reason. Their decision will not affect the standard of care they receive from any medical services at any time. Identifiable data already collected with consent would be retained and used in the study. No further data would be collected but the individual would be approached at follow-up.

### Outcomes

#### *In-vitro* Phase

Primary outcome: to develop and integrate an automated transdiagnostic risk calculator into the local electronic health register;Secondary outcome: to externally validate the transdiagnostic risk calculator in an independent NHS Trust in the UK;

#### *In-vivo* Phase

Primary outcome: adherence of clinicians to the use of the transdiagnostic risk calculator (proportion of clinicians who have responded to the prompts sent on the recommendation of the transdiagnostic risk calculator).Secondary outcome: impact of different types of alerts on the clinicians' adherence to the recommendations made by the transdiagnostic risk calculator.Secondary outcome: raw number of referrals initiated from secondary mental health care clinicians for an assessment of psychosis-risk.Secondary outcome: qualitative reasons for any lack of clinicians' adherence.

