## Abstract

**Background:** Primary indicated prevention in individuals at-risk for psychosis has the potential to improve the outcomes of this disorder. The ability to detect the majority of at-risk individuals is the main barrier toward extending benefits for the lives of many adolescents and young adults. Current detection strategies are highly inefficient. Only 5% (standalone specialized early detection services) to 12% (youth mental health services) of individuals who will develop a first psychotic disorder can be detected at the time of their at-risk stage. To overcome these challenges a pragmatic, clinically-based, individualized, transdiagnostic risk calculator has been developed to detect individuals at-risk of psychosis in secondary mental health care at scale. This calculator has been externally validated and has demonstrated good prognostic performance. However, it is not known whether it can be used in the real world clinical routine. For example, clinicians may not be willing to adhere to the recommendations made by the transdiagnostic risk calculator. Implementation studies are needed to address pragmatic challenges relating to the real world use of the transdiagnostic risk calculator. The aim of the current study is to provide *in-vitro* and *in-vivo* feasibility data to support the implementation of the transdiagnostic risk calculator in clinical routine.

**Method:** This is a study which comprises of two subsequent phases: an *in-vitro* phase of 1 month and an *in-vivo* phase of 11 months. The *in-vitro* phase aims at developing and integrating the transdiagnostic risk calculator in the local electronic health register (primary outcome). The *in-vivo* phase aims at addressing the clinicians' adherence to the recommendations made by the transdiagnostic risk calculator (primary outcome) and other secondary feasibility parameters that are necessary to estimate the resources needed for its implementation.

**Discussion:** This is the first implementation study for risk prediction models in individuals at-risk for psychosis. Ultimately, successful implementation is the true measure of a prediction model's utility. Therefore, the overall translational deliverable of the current study would be to extend the benefits of primary indicated prevention and improve outcomes of first episode psychosis. This may produce significant social benefits for many adolescents and young adults and their families.

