### *In-vivo* Phase

This phase will consist of a prospective feasibility study to test the real world usability of the transdiagnostic risk calculator to detect individuals at risk of psychosis at scale in clinical routine.

During this phase, a prototype will be made freely available to clinicians working in secondary mental health teams. In practice, clinicians will not be required to enter any new variables because all the predictors are already available as part of the standard clinical practice. In the first step (see step 1, Flow chart), the research team will screen potential patients meeting our study criteria using de-anonymised electronic health register data (CRIS). The data for these patients will be accessed by the study team to screen potential participants with the transdiagnostic risk calculator. The electronic health register will also be used to identify the responsible clinician for any individuals who are at risk as determined by the pre-defined threshold (established during the *in-vitro* phase).

The research team will then contact the responsible clinician through manual alerts (e.g., emails) and phone contact, recommending the patient be referred for a refined psychosis assessment. If an individual does not reach the threshold, the calculator will recommend no further assessment and standard care will be offered as usual. If possible, these alerts will be automatised during the study. During the second step (step 2, Flow Chart), the responsible clinicians will then decide whether to initiate the referral or not. A crucial outcome to be investigated will be the impact of different types of alerts on the clinicians' adherence on the use of the transdiagnostic risk calculator. If the individual is not referred for further assessment, standard care will be offered as usual. In the case the participant is referred for further assessment, the clinician will ask the patient if they consent to their details being given to the research team. If they do, the individual will be contacted by the research team and the procedure for collecting informed consent will be initiated.

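### The in-vivo primary outcome counts clinicians who responded to a prompt, but the stated aim is adherence to the recommendation to refer, and nothing excludes a reply that declines

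*Protocol article*

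**What the plan says.** Four parts of the protocol article bear on this point.

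- **Aim.** The Abstract (Method) describes the in-vivo primary outcome as "clinicians' adherence to the recommendations made by the transdiagnostic risk calculator (primary outcome"). The Sample Size section says that the key rate-limiting barrier "is the clinicians' adherence to the recommendations made by the calculator itself", and derives the choice of primary outcome from that.
- **Recommendation.** Under Design, In-vivo Phase, the research team contacts the responsible clinician by alert, "recommending the patient be referred for a refined psychosis assessment". At step 2, "the responsible clinicians will then decide whether to initiate the referral or not".
- **Event counted.** The Outcomes section gives "adherence of clinicians to the use of the transdiagnostic risk calculator (proportion of clinicians who have responded to the prompts". The Sample Size section repeats it: "defined by the proportion of clinicians who have responded to the prompts sent on the recommendation of the electronic risk calculator". Neither place says what counts as a response.
- **Referral itself.** It is a secondary outcome, stated as "raw number of referrals initiated from secondary mental health care clinicians for an assessment of psychosis-risk". Types of Data, under Data Management, also lists raw counts of at-risk cases detected, of referrals made and of individuals meeting CHR-P criteria.

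**The concern.** Responding to a prompt and following the recommendation are different events. The design separates them: the alert arrives, and the clinician then decides for or against referral. The aim concerns the second event, but the primary outcome is worded as the first. On that wording nothing excludes a reply that declines to refer.

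The uncertainty carries over to two secondary outcomes. The comparison of alert types and the qualitative reasons for lack of adherence both depend on the word adherence. A clinician who replies and declines could be adherent under the primary definition and yet be asked for reasons for non-adherence.

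At stake is the meaning of the study's headline figure. The in-vivo phase is meant to estimate how often clinicians act on the calculator, so that resources for routine use can be planned. A response rate is an upper limit for that quantity and may lie well above it.

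**Working it through.** **1. Reproduce the plan's own precision figure.** Inputs from the Sample Size section: at least 120 at-risk individuals detected, a maximum 95% margin of error of 0.1, adherence above 60%, and half of clinicians assumed to respond. Formula: half-width = 1.96 × √(p(1−p)/n).

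- n = 120, p = 0.6: 1.96 × √(0.24/120) = 0.0877
- n = 120, p = 0.5: 1.96 × √(0.25/120) = 0.0895
- n = 60 (half of 120), p = 0.6: 1.96 × √(0.24/60) = 0.124

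The ±0.1 figure is reproduced when all 120 detected individuals form the denominator. It is not reproduced at 60% adherence if only 60 do. The 120 are patients, whereas the outcome is worded as a proportion of clinicians.

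**2. Compare the two events.** Let r be the response rate and s the share of responders who decide to refer. Assume that every referral is preceded by a response and, for this illustration, that each clinician receives one alert. The primary outcome then equals r and adherence to the recommendation equals r × s. The protocol gives no value for s, so the full range is shown.

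| Share of responders who refer (assumed) | Primary outcome at r = 0.60 | Adherence to recommendation | Primary outcome at r = 0.50 | Adherence to recommendation |
|---|---|---|---|---|
| 100% | 60% | 60% | 50% | 50% |
| 75% | 60% | 45% | 50% | 37.5% |
| 50% | 60% | 30% | 50% | 25% |
| 25% | 60% | 15% | 50% | 12.5% |
| 0% | 60% | 0% | 50% | 0% |

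The primary outcome does not change with s. At 60% response and s = 75%, the gap is 60 − 45 = 15 points, larger than the half-width of about 8.8 points. At s = 100% there is no gap.

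**3. Precision after the change.** With referral as the event and 120 alerted cases as the denominator, the half-width is largest at p = 0.5, where it is 0.0895. The ±0.1 target holds at any rate if alerts are independent.

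**4. Room for clustering.** A half-width of 0.1 at p = 0.5 needs 1.96² × 0.25/0.01 = 96.04 independent cases. So 120 cases tolerate a design effect of 120/96.04 = 1.25 before the target is missed at that rate. The protocol does not say how many alerts one clinician may receive, so the actual design effect is unknown.

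**The case against.** The best defence is that the protocol leaves the word responded undefined, so it may have been meant as acting on the prompt. Collecting reasons for lack of adherence supports this, since a reason for not referring fits best if declining counts as non-adherence. Measuring engagement with alerts first, with referral as a secondary outcome, is also a defensible choice for a feasibility study. The first argument stands in part: the protocol does not expressly count a refusal as adherent, and a reader who infers that it does goes further than the text. But the mismatch remains. The aim names the recommendation, while the definition names a response to the prompt, in two sections. If referral was meant, the wording needs correcting; if engagement was meant, the aim does.

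Three stronger readings are tempting but not supported.

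- **That the referral count cannot repair the problem.** Types of Data lists both detected cases and referrals, and the clinician of each person over the threshold is to be contacted. Referrals per detected case can therefore be derived. The protocol does not specify that ratio, and it is not the primary outcome.
- **That patient refusals would be booked as clinician non-adherence.** The In-vivo Phase section says that the patient's details reach the team only with the patient's agreement. It does not say that the team learns the clinician's decision only then; the team is in direct email and phone contact with clinicians.
- **That a high response rate would be declared a success.** The article sets no success threshold, and the Analysis section describes the evaluation as exploratory.

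**Conclusion.** The point holds as a mismatch between the stated construct and the stated definition of the only in-vivo primary outcome. This is not detail left to an analysis plan, because the protocol fixes a definition that does not match its own aim. Followed as written, the primary rate can exceed adherence to the recommendation. The documents do not allow the excess to be computed: at 60% response it is 0 points if all responders refer, 15 if 75% do and 30 if 50% do. These shares are assumptions, and the figures also assume that every referral follows a response and that each clinician has one alert. The data the protocol already plans to collect would allow a referral rate, so the defect can be repaired without a larger sample.

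**What to change.** - Define in-vivo adherence as the number of alerted cases for which the clinician decided to refer, divided by all alerted cases. Count each case once, however many emails or calls it generated. Record the clinician's decision at step 2.
- Report any response to the prompt separately, as a process measure, and say what counts as a response.
- Report referrals over the detected-case count already listed under Types of Data, not only as a raw number.
- Use the same definition in the Abstract, the Sample Size section and the Outcomes section. It then also fixes the event for the alert-type comparison and for the reasons for non-adherence.
- State openly that the unit changes from clinicians to alerted cases, and compute the interval allowing for clustering by clinician.

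**Cost.** Recruitment for the in-vivo phase began on 1 August 2018 (Study Status), so this is an amendment to a running study. If it is classed as substantial, the Ethics and Regulatory Approval section requires a favourable ethics opinion before it is implemented. The headline rate may look less favourable, and the interval will be somewhat wider under clustering. The sample-size target need not change if the design effect stays at or below about 1.25.

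### The in-vivo primary outcome counts clinicians, but alerts and the sample size count patients, so a clinician with several alerts and mixed responses has no defined score

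*Protocol article*

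**What the plan says.** The outcome is stated twice with the clinician as its unit. The Outcomes list (In-vivo Phase) gives the "proportion of clinicians who have responded to the prompts sent on the recommendation of the transdiagnostic risk calculator". The Sample Size section has adherence "defined by the proportion of clinicians who have responded to the prompts sent on the recommendation of the electronic risk calculator".

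The Design section (In-vivo Phase) generates prompts by patient. The register is used to "identify the responsible clinician for any individuals who are at risk as determined by the pre-defined threshold", and the research team will then "contact the responsible clinician through manual alerts (e.g., emails) and phone contact, recommending the patient be referred". The clinician decides on referral of that patient. Nothing limits a clinician to one flagged patient over the 11 months.

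The Sample Size section moves between the two units. It counts patients ("we expect to detect at least 120 at-risk individuals per 11 months recruitment in SLaM"), assumes a response from clinicians ("Conservatively assuming that only half of SLaM clinicians would eventually respond to the alerts generated by the calculator"), and gives a "maximum margin of error of 0.1" for clinician adherence above 60%. The article states neither the number of clinicians nor the expected alerts per clinician.

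**The concern.** A proportion of clinicians needs one status per clinician. A clinician with one alert, or with several answered alike, has an obvious status. A clinician with two or more alerts who answers some and not others does not: 'responded to at least one' and 'responded to all' both fit the wording.

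Adding either rule would settle the scoring but leave a second problem. With unchanged behaviour per alert, an 'any' rate rises and an 'all' rate falls as alerts per clinician increase. Alert volume depends on caseload, on study length and on the risk threshold, which the article leaves to be tuned in the in-vitro phase. The Methods introduction says the feasibility figures are needed to estimate resources such as staffing for routine use. A rate that shifts with alert volume would not carry over to a service with a different number of alerts per clinician.

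**Working it through.** **The plan's own precision figure.** The 95% half-width is 1.96 × √(p(1−p)/n).
- n = 120, p = 0.6: 1.96 × √(0.24/120) = 0.088. At p = 0.5, the worst case, it is 0.090.
- n = 60 (if 'half' reduces the count), p = 0.6: 1.96 × √(0.24/60) = 0.124. It reaches 0.1 only at p of about 0.81.

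A bound of 0.1 is therefore met with n = 120, but only if each flagged patient counts as one independent clinician. The condition of adherence above 60% is then not needed. Whether 120 suits the stated margin is a separate question. What matters here is that the calculation uses patients as the denominator of a clinician proportion.

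**Same number of alerts for every clinician.** Let p be the response probability per alert, m the alerts per clinician and ρ the within-clinician correlation (beta-binomial). With independent responses, 'any' = 1 − (1−p)^m and 'all' = p^m. At p = 0.5, the plan's assumed response:
- m = 1: 50% and 50%, gap 0.
- m = 2: 75% and 25%, gap 50 points.
- m = 3: 87.5% and 12.5%, gap 75 points.

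Behaviour per alert is the same in all three lines. For m = 2 with correlation, the gap is 2p(1−p)(1−ρ). At p = 0.5 this is 25 points for ρ = 0.5 and 10 points for ρ = 0.8.

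**120 alerts spread at random over K clinicians.** K is assumed, because the article does not give it. Alerts per clinician are approximately Poisson with mean λ = 120/K, and only clinicians with at least one alert are counted. At p = 0.5 and ρ = 0:
- 'any' = (1 − e^(−λ/2)) / (1 − e^(−λ)) = 1 / (1 + e^(−λ/2)), and 'all' = 1 − 'any' by symmetry.
- The share of prompted clinicians with two or more alerts is 1 − λe^(−λ) / (1 − e^(−λ)).

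The ρ = 0.5 column comes from simulated allocations.

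| K | λ | Two or more alerts | 'Any' | 'All' | Gap, ρ = 0 | Gap, ρ = 0.5 |
|---|---|---|---|---|---|---|
| 60 | 2 | 69% | 73% | 27% | 46 points | 23 points |
| 120 | 1 | 42% | 62% | 38% | 24 points | 12 points |
| 240 | 0.5 | 23% | 56% | 44% | 12 points | 6 points |
| 400 | 0.3 | 14% | 54% | 46% | 7 points | not run |
| 480 | 0.25 | 12% | 53% | 47% | 6 points | 3 points |

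At p = 0.6 the simulated gaps are nearly the same: 45 to 23 points for K = 60, 24 to 12 for K = 120 and 12 to 6 for K = 240, as ρ goes from 0 to 0.5.

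**The case against.** **Size.** A reader might infer that the two rules necessarily give rates tens of points apart. The article does not support that. It gives no clinician count, and the Design section pilots in all secondary services of four boroughs, so a large pool cannot be excluded (the Inclusion Criteria name Lambeth only). The gap may be a few points, or none. This objection stands, and the size is given as conditional. In the other direction, 120 is stated as a minimum, and uneven caseloads would concentrate alerts on fewer clinicians.

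**Scoring.** A reader might also infer that the outcome cannot be scored at all. Only clinicians with two or more alerts and mixed responses lack a score. All others score the same under either rule.

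**Comparison with the margin.** It is tempting to say that the gap exceeds the plan's 0.1. That sets a distance between two readings against a half-width, and how often it is true depends on which values of K are tried. Each reading departs from the assumed 50% by only half the gap. No conclusion here rests on that comparison.

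**Left to a fuller document.** A counting rule for repeated prompts could sit in a full protocol or analysis plan, and sizing on 120 patients hints at one unit per alert. But the article does not omit the definition. It states it twice, with clinicians as the unit, and a per-alert analysis elsewhere would depart from that wording.

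**Consequences.** The study is exploratory, and no adherence cut-off governs roll-out. The Types of Data section lists at-risk cases detected and referrals made, which gives a patient-level referral proportion. That lessens the harm, but referral is not the same as response. The share of clinicians who engage is also a legitimate implementation measure, so it should still be reported, though not as the primary rate.

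**Conclusion.** The point holds as a mismatch of units. The primary outcome is a proportion of clinicians, prompts are issued per patient without limit per clinician, and precision is based on 120 patients. Mixed responders have no defined score, and either natural clinician-level rule gives a rate that depends on alert volume.

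The size rests on assumptions about the number of clinicians and the within-clinician correlation. At 50% response per alert with random spread, the gap runs from 46 points (60 clinicians, independent responses) to about 3 points (480 clinicians, correlation 0.5), and it is zero if each clinician has one alert. The documents do not show where in that range the study lies.

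**What to change.** In the Sample Size section and the Outcomes list, define the primary outcome per alerted patient: flagged patients whose responsible clinician responded, divided by all flagged patients for whom an alert was sent. Count repeat e-mails or calls about one patient as one alert. State what counts as a response, for example whether a reply is enough or a referral is needed; otherwise the numerator stays open. Give the 95% CI with a cluster-robust variance by clinician. Report the share of clinicians who answered none, some or all of their alerts as a descriptive secondary result.

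This needs no new data and brings the outcome into line with the 120 individuals already used for sizing. One cost is a wider interval. As an illustration, with two alerts per clinician and correlation 0.5 the design effect is 1 + (2 − 1) × 0.5 = 1.5, so the half-width at 50% goes from 0.0895 to 0.0895 × √1.5 = 0.110. The other cost is procedural. The Study Status section says in-vivo recruitment began on 1 August 2018, and the Ethics section requires a favourable opinion before a substantial amendment is implemented, so the change may need a protocol amendment.
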